#### Knowledge Assessments

##### Health Knowledge

A validated, general health knowledge test called the Heart Disease Fact Questionnaire [33] will be used. It assesses knowledge of cardiovascular health in a true/false/do not know questionnaire with 25 questions. There is a paucity of general health knowledge assessments that are validated. This tool is one of the few that provides a range of topics to assess participants’ knowledge and has been used in a previous study involving Deaf individuals.

##### Language Fluency

As Deaf individuals reside in communities that use English as the *lingua franca* (or *de facto* language), they are frequently bilingual. Fluency will be assessed in both ASL and English for the Deaf participants. English will be assessed for the hearing participants. ASL fluency will be tested with the *American Sign Language Sentence Reproduction Test* (ASL-SRT) [34], which is a brief global measure of individuals’ receptive and expressive ASL skills. Participants are required to watch videos of 20 ASL sentences and correctly reproduce the sentences after each one is presented. Correct reproductions are awarded 1 point, and the maximum total score is 20. ASL-SRT has been used in other cognitive science and psycholinguistic studies [36,37] and has been adapted to other signed languages. The ASL-SRT interrater reliability coefficient is 0.83, with an internal consistency (Cronbach alpha) of .88. CConstruct validity was established by illustrating that Deaf adults perform better on this test than Deaf children (*P*<.001; partial eta sq=.042) and native signers perform better than nonnative signers (*P*<.001; partial eta sq= 274). An equivalent and parallel test is available that assesses the receptive and expressive spoken English abilities that will be used for hearing participants. The test is called *Speaking Grammar Subtest of the Test of Adolescent and Adult Language, Third Edition* (TOEL3) [35], and has been widely used for language fluency assessments. The TOEL3 has internal consistency (Cronbach alpha) of .95, with test-retest reliability coefficient of 0.80.

Sociodemographic information will be based on an existing shortened version of the Behavioral Risk Factor Surveillance Systems [41]. This will be used to evaluate key demographic information for each participant and adjust for covariates in health literacy. For Deaf participants, additional questions will be asked to provide information on the following: (1) presence of Deaf family members, (2) ownership of a hearing aid or cochlear implant, (3) hearing status with and without a hearing aid or cochlear implant, (4) onset of hearing status, (5) any cultural identity with their hearing status, (6) Deaf school attendance, and (7) socialization preferences based on hearing status (Deaf, hearing, or both). We will also perform a Shoebox Audiometry [42] on all participants to assess their unaided hearing levels (HLs) from (−)10 dB to 90 dB at 500 Hz, 1000 Hz, 2000 Hz, and 4000 Hz for each ear. Shoebox is a leading tablet-based audiometer, which is a class 2 medical device registered and listed with the Food and Drug Administration. It offers a clinically validated, self-administered, automated testing platform optimized for use outside of a sound booth; can be completed in 5 min or less; and is completely configurable. HL will be defined by the standard greater than or equal to 25 dB average loss across the 4 frequencies in the better ear [43]. This will allow us to control for hearing loss variations among participants, especially because they may influence the level of access to information.

### Procedures

Once the participants are eligible, the research team will schedule an in-person visit to review both the informed consent and administer the different measures. This was done in the same fashion at each performance site. The research staff review the consent form and the brief study information directly in the participant’s preferred language (eg, ASL if Deaf). Once consent is obtained, the staff then proceeds with the data collection protocol. The measures are grouped into the following categories: (1) demographics/background information (includes Shoebox Audiometry), (2) interviewer-administered questionnaires (ie, cardiovascular knowledge assessment, self-efficacy, Web-based health information use, and e-literacy), (3) computer-administered measures (ASL-SRT, TOEL-3, and the ASL-NVS), (4) booklet testing (ie, CTT, KBIT2, and TOSCRF-2), and (5) Tobii eye tracker experiment. To avoid any ordering bias, the categories (except for the demographic/background information) are randomized to each participant (see Multimedia Appendix 1). The computer-generated randomization was completed before any participant recruitment. The counterbalance checklist designed with 4 blocks (A, B, C, and D) was randomly assigned to each participant (eg, 1 participant may get a checklist C that starts with booklet testing).

#### Procedures for Return Visit (for Those to Be Invited)

There will be 2 parts when the participant returns for their second visit (see Table 2). The first step will observe how participants search and acquire Web-based health information. This task performance will include 4 brief clinical vignettes (ie, pneumonia, deep vein thrombosis, migraines, and appendicitis) and multiple-choice answers will serve as a prompt. This will be given to all invited aim 3 participants to examine their abilities to search for health information on the Web and acquire health knowledge. Participants’ query formulations, navigation patterns, cursor activity, total search times, and number and nature of websites accessed to address the clinical vignettes will be recorded and assessed through the use of the Tobii usability testing software already available in our facilities [44]. The data will include video footage of the participant (including eye movements and facial expression), websites visited, duration of page visited, and number of clicks and cursor activity. The use of the Tobii provides several benefits: (1) the tool provides real-time dual-screen recording and display of both the participant’s actions online and webcam recordings of their facial expressions and eye movements; (2) the interviewer can watch the actions of the participant on the interviewer’s computer screen through the use of the Tobii Pro Studio software program in real time; (3) the interviewer can tag different-colored annotations (eg, search queries, websites accessed, and challenges encountered) to the video data being recorded, which is visible on the time bar; (4) the tool can instantaneously compute summary statistics such as the total search time in seconds, the number of unique websites and pages visited, and the number and characteristics of queries issued for the interviewer to discuss with the participant; and (5) the interviewer can scroll quickly to the relevant time of the video to help the participant observe and remember their actions but, more importantly, allow for the interviewer to ask more detailed questions on how and why specific actions were chosen and the participant’s thought process related to the online information. A figure demonstrating the different components and how it works can be accessed at Tobii website.

The recordings from the task performance above will serve as a prompt for the elicitation interview. It will help inform the subsequent qualitative assessment to help explain the quantitative results (of aims 1 and 2) and elucidate how and why Deaf individuals access and understand health information. Similarly, the same approach will be conducted with a subsample of hearing individuals. This will be done to provide robust comparisons. Video-based and semistructured qualitative assessments will be used to determine both how and why Deaf and hearing participants of different health literacy strata (inadequate and adequate; n=15 each) may differ in their performances with Web-based health information searches. The findings here will be used to help explain results from aims 1 and 2. The elicitation interview questions will be generated initially from the findings in aims 1 and 2 and complemented with additional questions following completion of the task performance on a computer. The interviewer will playback the dual-screen recording of the participant’s actions to facilitate recall of his or her own actions and thoughts with each task undertaken. The interviewer will encourage the participant to make his/her thoughts transparent, that is, telling how and why the choices were made in a narrative format. The dual-screen recording with performance metrics will serve as stimulus material for the video elicitation interview. As the dialog between the interviewer and the participant will be in ASL (visual language), a separate external video camera will be used to record this interaction for later transcription. The interview will reveal the complex cognitive and decision-making processes that may occur with each individual, which are not adequately revealed in earlier statistical analysis. The incorporation of both steps provides better integration of the findings of all 3 aims and generates robust data to guide future intervention development to address inadequate health literacy and information marginalization for Deaf populations. A strength of this step is the ability to explore contextual factors (ie, task- and user-oriented factors) that could not be explained with the first visit. As stated by a newer eHealth literacy model [45], these task- and user-oriented factors are important in their roles in the overall eHealth context. The proposed step will help examine how these intrapersonal and system-based factors may shape the Web-based health experience and abilities for both Deaf and hearing individuals.

**Table 2 table2:** Aim 3 approaches.

Definition	Purpose	Approach	Data collection	Expected outcomes
Web-based health information navigation and comprehension (step 1)	To assess Web-based health information search ability, acquisition, and patterns	Use of Tobii video/online use recording software; 4 clinical vignettes with questions to prompt Web-based search	Navigation patterns of Deaf individuals; preferences of health websites, including search engines (n=15 Deaf and n=15 hearing for comparison); scoring on questions related to vignettes	Assess Web-based health information search ability of Deaf individuals (unknown); determine if Deaf individuals’ health literacy determines the quality of the navigation and comprehension of the information (unknown); generate areas of weaknesses and strengths for interventions to focus (unknown)
Elicitation interviews (step 2)	To explain and expand the understanding of the findings demonstrated in aims 1 and 2	Use of elicitation interviews about video recordings of the participants and their Web-based searches	Explore how and why participants decided to use the websites they chose, including the types of queries and what aspects of the Web-based information was useful to them	Assess how Deaf individuals visualize and learn Web-based health information (unknown); determine the preferences of health information tools and dissemination (unknown) and understand why they have those preferences (unknown)

### Statistical Analyses for Aim 1

Frequency statistics will be used to summarize categorical data, whereas means (SDs) were computed to describe continuous data. Correlations between main study variables will also be analyzed using Pearson r correlation coefficients. Differences between the Deaf and hearing participants in terms of ASK related to health information will be assessed using linear regression models. To control for the effects of demographic and physiological covariates on the dependent variables of ASK related to health information, sociodemographic (eg, race) and physiological factors (ie, hearing loss severity and laterality) will be entered in model 1 as potential confounding factors affecting each variable of interest. As we are primarily interested in the additional effects of ASK related to health information on health literacy and eHealth, predictor variables will be subsequently entered in model 2. Differences between the Deaf and hearing participants in terms of ASK related to health information will be assessed using linear regression models. The scales for each modality described in Table 1 will be used as a separate outcome with Deaf versus hearing as the primary covariate. A propensity-adjusted analysis will also be conducted with the propensities defined as the predicted probability of having adequate health literacy as a function of sociodemographic factors estimated through a logistic regression model. For observational data, the propensity-matched methods are often deemed to be a better alternative to the usual multiple linear regression controlling for potential confounders. Strata based on propensity quantiles will be used as a categorical covariate in the linear regression model. Furthermore, the variability across sites will be controlled for in the model. Usual model diagnostics will be performed, followed by corrective actions as necessary.

### Statistical Analyses for Aim 2

The ASL-NVS and the English-NVS will be used to assess the health literacy score in both Deaf and hearing participants, respectively. The health literacy indicator (ASL-NVS) ranges in value from 0 to 6. To understand whether the association between health literacy and ASK related to health information differs between Deaf and hearing individuals, we shall compute in the Deaf and hearing groups Fisher Z-transformed partial correlations between health literacy and each of the constructs, adjusted for the socioeconomic factors and potential site differences. Subsequently, 2-sample Z-test of these correlations will be carried out for each construct. We shall supplement this analysis with a regression approach where health literacy will be regressed on the group and each of the constructs along with their interaction controlling for the socioeconomic factors and site. Although the interaction term is of primary focus, such a model will provide an overall appraisal of the association between health literacy and various covariates. On the basis of PI’s previous work involving the ASL-NVS, one can alternatively characterize health literacy as a categorical variable with categories of adequate (NVS score of 5-6), indeterminate (2-4), and inadequate (0-1). As a secondary analysis, we will conduct an ordinal logistic regression with the categorical outcome of health literacy using the same covariates in the model as mentioned above.

### Analyses for Aim 3

Building on the methodology used in previous Web-based search behavior studies [46], participants’ search skills and success in addressing the clinical scenario tasks will be assessed using a combination of methods. First, based on the browser log and interaction data gathered by the usability software, we will compute summary statistics, such as the total time (in minutes) spent in searching, the number of unique websites and pages visited, and the number and characteristics of queries issued, involved in completing each task. Second, we will include time-based retrieval measures [47] that can characterize and quantify how a participant’s search progress evolves over time. Knowledge acquisition will be measured by the number of correct responses based on the clinical vignettes (score range between 0 and 12). All measures representing navigation skill and knowledge acquisition will be compared across levels of health literacy (adequate vs intermediate/inadequate) on the subgroup of the preselected 30 Deaf participants using 2 sample *t* tests. Although it is anticipated that power will be low to observe statistical significance, the primary objective for this comparison is to identify trends. Search progress for the clinical scenarios will be defined in terms of the quality of health information pages found during the search task. To assess the quality of health information pages, the research team will evaluate the Web pages/resources returned by participant searches or visited by the participant via browser navigation in terms of accuracy and coverage of the target facts in the reference set. Any differences will be discussed until a consensus is obtained.

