## Methods

### Overview

For this study, there are 3 proposed aims. Aim 1 is to evaluate differences in ASK, regarding health information for both Deaf signers and hearing English speakers. Aim 2 plans to assess hearing status as an effect modifier of the association between health literacy and ASK with health information. Aim 3 will qualitatively assess the impact of health information accessibility and patterns of use on health literacy with one-on-one elicitation interviews. This will be based on actual Web-based health information searches for 4 clinical vignettes using an observed task fulfillment experiment as a prompt. The goal of this aim is to explore differences with Web-based health information search ability and health knowledge acquisition in a subsample of Deaf and hearing individuals recruited from aims 1 and 2. The University of Michigan institutional review board (IRB) approved the study and provides coordination with the following IRBs: Sinai Hospital, Rochester Insitute of Technology, and Hurley Medical Center (HMC). The study is also registered at the ClinicalTrials.gov under ID NCT03093779.

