### Eligibility Criteria

To be eligible, study participants must be aged at least 18 years. For the Deaf study group, eligible Deaf participants must identify themselves as Deaf and communicate primarily in ASL. For the hearing comparison group, the hearing study participants also must be aged at least 18 years but self-report normal hearing and communicate in spoken English (ie, English monolinguals). Participants will be excluded if they have any cognitive impairments (eg, because of dementia, delirium, or intoxication), inability to consent to the study, or limited vision.

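### Aim 1, on its most natural reading, adjusts the Deaf-versus-hearing comparison for hearing loss severity and laterality, which are not confounders of that comparison

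*Protocol article*

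**What the plan says.** The Overview in Methods sets the target: "Aim 1 is to evaluate differences in ASK, regarding health information for both Deaf signers and hearing English speakers".

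Statistical Analyses for Aim 1 first says that Deaf-hearing differences in ASK will be assessed by linear regression. The next sentence opens "To control for the effects of demographic and physiological covariates on the dependent variables of ASK related to health information" and goes on to state that sociodemographic factors and "physiological factors (ie, hearing loss severity and laterality) will be entered in model 1 as potential confounding factors affecting each variable of interest". A model 2 follows, which adds predictors because interest lies in what ASK contributes to health literacy and eHealth. The paragraph then returns to the group comparison: "The scales for each modality described in Table 1 will be used as a separate outcome with Deaf versus hearing as the primary covariate". It also plans an analysis using propensity strata built from sociodemographic factors, control for site, and model diagnostics.

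Under Eligibility Criteria, "eligible Deaf participants must identify themselves as Deaf and communicate primarily in ASL", while hearing participants must "self-report normal hearing and communicate in spoken English". Neither group has an audiometric threshold.

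In Measures, the paragraph on sociodemographic information and audiometry plans unaided testing of every participant from -10 to 90 dB and gives the reason: "This will allow us to control for hearing loss variations among participants, especially because they may influence the level of access to information".

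**The concern.** A confounder of the Deaf-hearing contrast would be a factor outside the exposure that affects both group membership and ASK. Hearing loss severity does not fit. One group is selected on self-reported normal hearing and the other is Deaf, so severity largely measures group a second time. The article's own reason for controlling it is that it may affect access to information, and the study's first objective is to explain the role of information marginalization. Severity is thus part of the mechanism.

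If severity and group are in the same model, two things follow. The group coefficient becomes the difference between Deaf and hearing people with the same hearing level, a narrower question than Aim 1 poses. And because few participants in one group may have hearing levels typical of the other, the estimate becomes imprecise and depends on the assumed shape of the severity term. A real Deaf-hearing difference could be reported as small or absent.

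**Working it through.** **1. Which model carries the covariates?** The sentence introducing severity and laterality names the ASK measures as the dependent variables and directly follows the sentence on Deaf-hearing differences. The later sentence takes the Table 1 scales as outcomes, with group as the main covariate. Read together, they describe one regression of ASK on group, adjusted for severity and laterality. No sentence lists group and severity as terms of the same model, so this is the most natural reading and not a certainty. Nothing confines the adjustment to the Deaf group.

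**2. The plan's own figure.** Sample Size gives 450 per group to detect a 20% difference between correlations, one-sided 1%, 80% power. With n = 2[(z(1-α) + z(power)) / (atanh r2 - atanh r1)]² + 3 and an assumed r of 0.1 versus 0.3 (the baseline is not stated):

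- 2[(2.326 + 0.842) / (0.3095 - 0.1003)]² + 3 gives 462 per group.
- At 450 per group the power is 78.8%.

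The figure is reproduced and is not at issue. It concerns correlations, the Aim 2 question. The same section says the size amply covers the Aim 1 group differences.

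**3. Aim 1 without hearing-loss covariates.** The detectable standardized difference is (1.960 + 0.842) × √(2/450) = 0.187, or 0.19 (two-sided 5%, 80% power).

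**4. Aim 1 with severity added.** The variance inflation factor (VIF) of the group coefficient is 1/(1 - r²), where r is the correlation between group and better-ear dB average. The standard error rises by √VIF, the information per group is 450/VIF, and the detectable difference is 0.187 × √VIF. The calculation takes severity as linear dB and holds residual variance fixed. All means and SDs are assumptions, with normal values clipped to -10 to 90 dB.

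| Hearing mean/SD | Deaf mean/SD | r | VIF | Effective n per group | Detectable difference |
|---|---|---|---|---|---|
| 18/15 | 70/25 | 0.81 | 2.9 | 157 | 0.32 |
| 15/12 | 75/20 | 0.90 | 5.1 | 88 | 0.42 |
| 15/10 | 80/20 | 0.92 | 6.8 | 66 | 0.49 |
| 12/10 | 80/15 | 0.95 | 10.1 | 45 | 0.59 |
| 10/8 | 80/12 | 0.97 | 15.5 | 29 | 0.74 |

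Truncating the distributions instead of clipping them lowers the middle row's VIF from 6.8 to 6.1. A still sharper separation (10/6 versus 85/8) gives 37; the conclusion does not rely on it.

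**5. Overlap.** In the two best-separated rows, at most 0.05% of hearing participants lie above the 1st percentile of the Deaf dB level. For 15/12 versus 75/20 the share is 12%, and for the deliberately wide case 67%. How far the adjusted contrast is an extrapolation therefore depends on data the documents do not give.

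**6. Understatement.** If a share f of the total group difference tracks severity, the coefficient left on group is total × (1 - f). For an assumed total of -0.8 SD, f of 25%, 50%, 75% and 100% leaves -0.6, -0.4, -0.2 and 0.

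**The case against.** **The paragraph joins two analyses.** Model 1 may be the first block of a sequence ending in health literacy and eHealth, where ASK and not group is the coefficient of interest. The later sentence on the group comparison does not repeat severity or laterality. This stands as an ambiguity, and a reader should not infer that the plan explicitly lists group and severity in one model. But the model 1 sentence itself names ASK as the outcome, so the wording at least permits the analysis described here.

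**Deaf is an identity and a language, not a dB level.** This also stands. A reader might infer that the adjustment removes the exposure itself. Eligibility rests on Deaf identity with primary use of ASL, and on self-reported normal hearing, with no threshold for either. Some overlap is possible, and a difference at equal hearing level is a coherent direct-effect question where overlap exists. It is not the question Aim 1 states.

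**Other safeguards exist.** The propensity analysis uses sociodemographic factors only, and diagnostics with corrective action are planned. The first gives a useful comparison but does not say which estimate is primary. A collinearity check may flag the imprecision, but it cannot show that a variable on the pathway has been adjusted for, and it leaves the choice until the data are seen.

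**The size is assumed.** Correct: every dB input is an assumption. The form in which severity enters is not stated, and added covariates may reduce residual variance.

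**Conclusion.** The concern holds in a limited form. On its most natural reading, Aim 1 adjusts the Deaf-hearing contrast for a near-proxy of group that lies on the pathway under study. That changes the question answered, can understate the difference, and costs precision. Under the stated assumptions the VIF is roughly 3 to 15 and the detectable difference rises from 0.19 to about 0.3 to 0.7. These figures are illustrative, but the direction holds even with wide overlap (VIF 2.9).

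Three stronger inferences are not supported. Collinearity alone inflates variance; it does not systematically reverse a coefficient, which would need misspecification or mediation. Aim 2 is not affected, since its models name socioeconomic factors and site and not hearing loss. And the stated sample-size calculation is not shown to be wrong; only its assurance for Aim 1 fails to account for this covariate.

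**What to change.** In Statistical Analyses for Aim 1:

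- State that the primary Deaf-hearing contrast for each ASK measure is adjusted for sociodemographic factors and site only, in line with Aim 2's use of socioeconomic factors and site.
- Separate this from the model 1/model 2 sequence for health literacy and eHealth, so that the terms in each model are clear.
- Use severity and laterality in secondary models within the Deaf group, or in a pooled analysis clearly labelled as a direct-effect or sensitivity analysis.
- Tie the Sample Size remark on Aim 1 to the model without these covariates.

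Audiometry is already planned for all participants and the article describes recruitment as underway, so only the analysis wording changes. The small downside is that the primary contrast no longer separates Deaf identity and ASL use from hearing level. The labelled secondary analysis can address that as far as overlap allows.

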## Introduction

### Background

Deaf American Sign Language (ASL) users are nearly 7 times more likely than their hearing peers to have inadequate health literacy [1]. Deaf ASL users (henceforth, Deaf) rarely receive language concordant health care services and are at highest risk for miscommunication with their health care providers. Deaf individuals understand less than 30% of what is being said through lipreading [2,3]. Furthermore, prose literacy poses a challenge for Deaf individuals; the average Deaf individual reads English at the fifth- to sixth-grade level [1,4-7]. The use of interpreters is the standard of care for Deaf ASL users, yet they are infrequently provided [8]. The majority of Deaf individuals (approximately 95%) have hearing family members who do not sign. Thus, many experience the *dinner table* syndrome, where they have encountered years at the dinner table watching close family members and friends converse with each other while being unable to understand what is being said, depriving them of incidental learning opportunities that many hearing individuals take for granted [9]. The loss of incidental learning opportunities and information marginalization for Deaf individuals occurs daily in a broad range of work, schools, friends, families, government, media, and health care contexts [1]. Many Deaf ASL users learn language, health information, and even culture via peers rather than family [10] and struggle to identify and correct misinformation [11]. Due to this communication-depleted milieu, inadequate health literacy may be an important cause of the lower level of health-related knowledge and worse health outcomes that have been observed among Deaf individuals.

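### The supplementary propensity analysis for Aim 1 models adequate health literacy, although the groups it compares are Deaf and hearing participants

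*Protocol article*

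**What the plan says.** The Overview of the protocol article sets the contrast: "Aim 1 is to evaluate differences in ASK, regarding health information for both Deaf signers and hearing English speakers". Under Statistical Analyses for Aim 1, each scale in Table 1 "will be used as a separate outcome with Deaf versus hearing as the primary covariate". The same paragraph first enters sociodemographic and physiological factors as potential confounders. It then adds a propensity-adjusted analysis, with the "propensities defined as the predicted probability of having adequate health literacy as a function of sociodemographic factors estimated through a logistic regression model".

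On how the score is used, it says: "Strata based on propensity quantiles will be used as a categorical covariate in the linear regression model". The reason given is that "propensity-matched methods are often deemed to be a better alternative to the usual multiple linear regression controlling for potential confounders".

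No propensity model for Deaf versus hearing status appears anywhere in the article. In Statistical Analyses for Aim 2, health literacy is the dependent variable: "health literacy will be regressed on the group and each of the constructs along with their interaction controlling for the socioeconomic factors and site".

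**The concern.** Stratifying on a propensity score removes confounding because, among people with the same probability of exposure, the covariates in the score are distributed alike in the exposed and the unexposed. That holds for the exposure being modelled. Here the exposure is Deaf versus hearing, but the modelled event is adequate health literacy. People in one stratum share a predicted chance of adequate literacy. Deaf and hearing people in that stratum can still differ in age, race or education.

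Confounding is plausible in this study. Participants are recruited through flyers, listserves, social media and outreach, and the article describes no matching of the two groups. Under Study Setting and Participants, Rochester is chosen partly for its highly educated Deaf community and Chicago partly for its minority community. Because the article presents propensity methods favourably, a reader may take the stratified result as a second, stronger confirmation of the Deaf-hearing difference. As defined, it is not built to give one.

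**Working it through.** **Step 1. Roles of the variables (Statistical Analyses for Aim 1).**

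- Contrast: Deaf versus hearing.
- Outcomes: the Table 1 scales. Health literacy is not among them; it is measured separately by the Newest Vital Sign.
- Event in the propensity model: adequate health literacy.

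For the Deaf-hearing comparison the score is therefore not a propensity score. It is not a prognostic score for those outcomes either. The article gives no figure for this analysis, and the sample size of 450 per group does not depend on it, so there is no stated figure to reproduce.

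**Step 2. Simulation inputs.** From the article: 450 Deaf and 450 hearing participants, and quantile strata as a categorical covariate in a linear model. Assumed: quintiles; two standard normal covariates x1 and x2; a shift of -0.5 SD in the Deaf group for one or both; outcome = 0·Deaf + 0.5·x1 + 0.5·x2 + standard normal error; logit of adequate literacy = h1·x1 + h2·x2 - 1.0·Deaf; 300 replicates. The true group difference is 0, so the mean group coefficient is the bias, in residual SD units. Share remaining = stratified bias / crude bias.

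| Setting | h1, h2 | Shifted by group | Crude | Literacy strata | Share | Deaf-status strata | Share |
|---|---|---|---|---|---|---|---|
| a | 0.7, 0.7 | x1, x2 | -0.499 | -0.049 | 10% | -0.046 | 9% |
| b | 0.9, 0.1 | x1, x2 | -0.509 | -0.191 | 38% | -0.056 | 11% |
| c | 0.1, 0.9 | x1 only | -0.248 | -0.183 | 74% | -0.026 | 10% |
| d | 0.9, 0.0 | x2 only | -0.247 | -0.213 | 86% | -0.022 | 9% |

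**Step 3. Why the bias remains.** The largest within-stratum Deaf-hearing imbalance under literacy strata was 0.063 SD in (a), 0.388 in (b), 0.469 in (c) and 0.486 in (d). Under Deaf-status strata it was at most 0.05 in every setting. Residual bias is about the sum of outcome coefficient × imbalance. In (d), taking the small x1 imbalance to run the opposite way, this is 0.5 × (-0.486) + 0.5 × 0.058 = -0.214, against -0.213 simulated.

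**Step 4. A second set-up, with education and age as confounders.** It also uses n = 900 and a true difference of 0. Education and age relate to both group and outcome; education, race and Deaf status drive literacy (400 replicates).

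- Crude bias: -0.403.
- Literacy strata: -0.224, and 0.224/0.403 = 56% remains.
- Deaf-status strata: -0.034, and 0.034/0.403 = 8% remains.
- Linear covariate adjustment: 0.003.

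The 56% depends on age not predicting literacy. In rebuilt versions (crude about -0.40), an age coefficient of 0.4 on the logit scale gave -0.07 to -0.10, and 0.8 gave about -0.05. Across versions, literacy strata ranged from -0.24 to -0.05, so 0.24/0.40 = 60% down to 0.05/0.40 = 12.5% remained. Deaf-status strata ranged from -0.03 to -0.05, or 7.5% to 12.5%.

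**Step 5. If the covariates stay in the model beside the strata.** Bias was then within 0.01 of zero.

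**The case against.** The strongest reply is about scope. The propensity analysis is an addition to a covariate-adjusted regression, which was essentially unbiased in these simulations (0.003). A reader might infer that Aim 1 as a whole is left confounded. The article does not support that: the main regression does not use the score, and neither do Aim 2 or the sample size. This part of the objection stands and limits the severity.

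A reader might also infer that literacy strata cannot balance the two groups. That is too strong. The score is a function of sociodemographic factors and removes some confounding. In setting (a), where the covariates predict literacy and Deaf status in the same proportions, it did as well as a Deaf-status score. The article itself expects sociodemographic factors to relate to health literacy (Study's Theoretical Framework) and names age and education as possible correlates (Study Design), which favours the milder end of the range. Nothing in the plan secures that condition, however.

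A third tempting inference starts from the Background statement that "Deaf American Sign Language (ASL) users are nearly 7 times more likely than their hearing peers to have inadequate health literacy": that a pooled literacy model absorbs the group effect and so worsens the bias. The check went the other way. With no age effect, raising the Deaf effect on literacy from 0 to 1 to 2 on the logit scale reduced the bias from -0.23 to -0.19 to -0.15, because the score moved closer to one for Deaf status.

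The article does not say that the strata replace the other covariates. Its wording about an alternative to regression suggests so, but if both were kept the problem would largely disappear. The claim of superiority is also hedged. Finally, the section's remarks on model 2 treat health literacy and eHealth as outcomes, so literacy is not foreign to Aim 1. It is still not the exposure in the comparison that the strata are meant to adjust.

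**Conclusion.** The definition is wrong for the stated contrast and should be fixed. The strata are not built to balance Deaf and hearing participants. Where they replace covariate adjustment, they can leave confounding in any factor that differs by group but predicts literacy weakly.

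With education and age as confounders, roughly 10% to 60% of the crude bias remained, against roughly 10% with a Deaf-status score. The shares of 74% and 86% in settings (c) and (d) arise when the only imbalanced factor predicts literacy barely or not at all, and mark the unfavourable extreme. All coefficients are assumptions, so these figures show direction and possible size; they do not forecast this study's data. The near-zero bias of the covariate-adjusted regression also rests on the simulated outcome being linear in the covariates. The consequence is confined to the supplementary analysis.

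**What to change.** In Statistical Analyses for Aim 1, redefine the propensity as the predicted probability of being Deaf rather than hearing, given sociodemographic factors and site, estimated by logistic regression. Keep the quantile strata as a categorical covariate, and check Deaf-hearing balance on the sociodemographic factors within strata. State whether the strata replace the model 1 covariates or are added to them.

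If adequate versus not adequate literacy was the intended contrast for this analysis, say so and make literacy the exposure in that model, reported separately from the Deaf-hearing comparison.

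The cost is one or two sentences and a balance table. Data collection, sample size and software do not change.
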